### 4.13. Patient and Public Involvement

Two consumers were involved in reviewing the research materials for the CT intervention. Participants will also provide feedback on intervention acceptability and satisfaction through exit interviews, which will inform refinement of the study for a future trial.

## 5. Discussion

This protocol describes a randomised, double-blind, sham-controlled feasibility pilot trial evaluating the combined delivery of iTBS and structured cognitive training in people with MCI. The study is designed to address the gap between preliminary evidence suggesting potential cognitive benefits from CT and neuromodulation and the practical requirements for implementing a combined intervention in a future definitive trial. By prioritising feasibility, acceptability, adherence, and safety, the study will assess whether the intervention can be delivered as planned in the target population and whether predefined progression criteria are met.

A key strength is the integration of a brief iTBS protocol with a structured CT program that transitions from supervised in-person sessions to home-based training, balancing standardisation and participant support with accessibility and real-world feasibility. The inclusion of EEG and TMS measures provides an opportunity to explore neurophysiological changes that may accompany cognitive change, providing insights into biological drivers of treatment responsivity, although these analyses are exploratory and not intended to establish definitive mechanisms.

Several limitations should be considered. First, the feasibility sample is not powered to detect definitive between-group treatment effects; cognitive and neurophysiological findings will therefore be interpreted as preliminary estimates to inform the design and sample size of a future adequately powered trial. Second, eligibility criteria required for participant safety, intervention delivery, and study standardisation may limit generalisability to the broader MCI population; requirements relating to age, English proficiency, handedness, digital access, and TMS eligibility may yield a sample that is healthier or more technologically able than the wider MCI population. Third, the mixed in-person and home-based delivery model may introduce variability in the context in which CT is completed, although online completion will be automatically recorded and adherence patterns monitored. Finally, because the intervention combines iTBS with a structured cognitive training program, psychoeducation, and remote support, any subsequent signals of cognitive change cannot be attributed to a single component.

Despite these limitations, the study is designed to provide practical evidence regarding recruitment, retention, adherence, acceptability, and safety, together with preliminary estimates of cognitive and neurophysiological outcomes, which will refine the intervention, outcome selection, delivery procedures, and sample-size assumptions for a future definitive randomised controlled trial.

## 6. Ethics and Dissemination

Ethical approval has been granted by the Western Sydney University HREC (H16500), and the study will be conducted in accordance with the National Statement on Ethical Conduct in Human Research and Good Clinical Practice guidelines. All participants will provide written informed consent before enrolment. Confidentiality will be ensured through secure data storage and de-identification in REDCap. Participants may withdraw at any time without consequence.

Findings from the trial will be disseminated through peer-reviewed publications, conference presentations and academic theses. A lay summary of results will be provided to participants following study completion.

## 7. Trial Registration

This trial was registered on 29 August 2025 with the Australia and New Zealand Clinical Trials Registry (ACTRN12625000952448): https://anzctr.org.au/Trial/Registration/TrialReview.aspx?id=390009 (accessed on 17 August 2026).

## 8. Trial Status

This trial is currently in the recruitment phase.

## Figures and Tables

**Figure 1 mps-09-00130-f001:**
[figure not shown]
Overview of the cognitive training progression across the 14 sessions of the iCog.X Boost Program.

**Figure 2 mps-09-00130-f002:**
[figure not shown]
Participant timeline for the iCog.X Boost Trial, illustrating screening and consent, randomisation, intervention, and assessment timepoints across 18 weeks.

**Figure 3 mps-09-00130-f003:**
[figure not shown]
CONSORT 2025 flow diagram of participant screening, enrolment, randomised allocation to the active and sham iTBS arms, and planned follow-up and analysis. Flow diagram beyond randomised count is intentionally left blank as the trial is currently ongoing.

**Table 1 mps-09-00130-t001:** Predefined feasibility indicators and stop/go decision criteria.

Indicator	Proceed	Proceed with Modifications	Do Not Proceed
**Recruitment-related variables**			
Recruitment rate	At least 2 participants per month can be recruited	At least 1 participant per month can be recruited	Less than 1 participant per month can be recruited
Eligibility yield	One or more in four screened participants meets eligibility criteria (≥25%)	At least one in six screened participants meets eligibility criteria	Less than one in six screened participants meets eligibility criteria
**Intervention-related variables**			
Adherence	≥80% of participants complete ≥ 80% of prescribed iTBS and CT sessions	≥65% of participants complete ≥ 80% of prescribed iTBS and CT sessions	<65% of participants complete ≥ 80% of prescribed iTBS and CT sessions
Tolerability	≥75% of withdrawals are not attributable to intervention-related adverse events	60–74% of withdrawals are not attributable to intervention-related adverse events	<60% of withdrawals are not attributable to intervention-related adverse events
Acceptability	≥70% of participants rate the intervention as acceptable or highly acceptable on post-intervention scale	50–69% of participants rate the intervention as acceptable	<50% of participants rate the intervention as acceptable

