### 4.4. Outcome Measures

Outcomes will be assessed at 5 timepoints: baseline (Week 0), post-iTBS (Day 5, Week 1), mid-intervention (Week 5), post-intervention (Week 10), and follow-up (Week 18). As this is a feasibility pilot trial, the primary outcomes are feasibility, acceptability, adherence, and safety. The predefined progression (“stop/go”) criteria in Table 1, spanning recruitment, eligibility, adherence, tolerability, acceptability, and retention, will determine whether to proceed to a full-powered definitive trial, while safety is monitored throughout. Each primary domain is operationalised below.

**Feasibility (recruitment and retention).** Recruitment feasibility will be reported descriptively, including the number of participants registering interest, the proportion screened, eligibility yield, and the time taken to reach the target sample; these indicators establish whether recruitment is viable within the study’s eligibility constraints ahead of a definitive trial. Retention will be expressed as the proportion of randomised participants completing the post-iTBS (Week 1), post-intervention (Week 10), and follow-up (Week 18) assessments, and it will be evaluated against the attrition thresholds in Table 1.

**Adherence.** Adherence will be quantified as the proportion of scheduled iTBS and CT sessions completed, against the predefined thresholds in Table 1. iTBS attendance will be verified against site logs, while home-based CT completion will be captured automatically through the online training platform on a per-session basis. Missed sessions and the reasons for non-completion will be documented, and patterns of adherence across the intervention period, including session completion over time, drop-off, and whether adherence differs between the initial in-person sessions and the subsequent home-based period, will be summarised descriptively.

**Acceptability.** Acceptability will be evaluated using a post-intervention satisfaction scale and semi-structured exit interviews examining perceived burden, comfort, and willingness to participate again, and will be judged against the acceptability threshold in Table 1.

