**Safety and tolerability.** Safety will be monitored at every iTBS session and throughout the follow-up period; participants will be asked to report adverse sensations (e.g., headache, scalp discomfort, tingling, and fatigue), and all adverse events (AEs) will be reviewed for severity and relatedness and managed in accordance with the safety procedures described in Section 4.10. Tolerability will be operationalised as the proportion of withdrawals that are not attributable to intervention-related AEs, and will be evaluated against the threshold in Table 1.

Secondary outcomes include cognitive measures of verbal memory (CVLT-II), and episodic memory (RBANS Story Recall), executive function and processing speed (D-KEFS TMT; WAIS-IV Coding, Similarities; Digit Span), functional independence (HBA-FAQ), psychological well-being (PHQ-9, GAD-7, PSQI), and health-related quality of life (EQ-5D-5L). All measures were selected based on clinical relevance and psychometric properties (Supplementary Table S1). These outcomes are exploratory and are included not to establish efficacy but to estimate the magnitude and variability of potential change and to inform outcome selection and sample-size estimation for a future definitive trial. Exploratory signals of change will be characterised using effect size estimates (Cohen’s d) with means, standard deviations, and 95% confidence intervals.

Tertiary outcomes are mechanistic and include neurophysiological measures of cortical excitability and inhibition using paired-pulse TMS paradigms, including short- and long-interval intracortical inhibition (SICI, LICI), resting-state EEG and event-related potentials (ERPs) recorded during cognitive tasks. Given the feasibility design, these neurophysiological measures are exploratory and hypothesis-generating. They are intended to determine which markers can be feasibly acquired and are worth retaining as mechanistic outcomes in a definitive trial.

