### 4.7. Sample Size

As this is a feasibility pilot trial, the sample size was not determined by formal power calculations for hypothesis testing. Sample size determination in pilot studies is typically based on practical considerations, study logistics, and precedent rather than statistical power, with 12 participants per group recommended as a reasonable minimum [48]. Feasibility and pilot trials using iTBS and rTMS in MCI have employed sample sizes ranging from 18 to 38 participants [49]. A sample of 44 participants (22 per group) is consistent with and exceeds these precedents, and is sufficient to characterise feasibility outcomes, estimate variability in cognitive measures, generate preliminary effect size estimates, and is expected to provide preliminary neurophysiological data to inform the design of a future definitive trial. An anticipated dropout rate of ~20% has been accounted for [50], and effect size estimates will build on a pooled effect size of g = 0.36 for CT in MCI [11] to inform a future definitive trial.

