**Attrition**			
Retention	<20% participant attrition at final follow-up (Week 18)	20–30% attrition at final follow-up	>30% attrition at final follow-up

**Table 2 mps-09-00130-t002:** Inclusion and exclusion criteria.

Inclusion Criteria	Exclusion Criteria
– Aged 55–85 years – MCI based on Winblad criteria [30] – Subjective cognitive complaints via a semi-structured clinical interview – Objective cognitive decline (M@T score 27–37) OR scoring at least 1.0–1.5 SDs below age-adjusted population norms and/or estimated premorbid ability based on the ToPF – Preserved or minimal iADL impairment based on the HBA-FAQ and study neuropsychologist discretion. – Right-handed (Edinburgh Handedness Inventory) – Fluent in English (reading, writing, speaking) – Normal or corrected-to-normal vision and hearing – Access to a personal desktop or laptop with full internet access	– Prior exposure to TMS within the past 12 months – M@T score < 27 – Study neuropsychologist discretion regarding cognitive and/or functional status based on neuropsychometric performance. – Current symptoms of major depression, defined as a PHQ-9 score ≥ 10 and meeting criteria for a current depressive episode on the MINI interview. – Contraindications to TMS [29]. – Alcohol consumption within 24 h of assessments – Current smokers – Low digital literacy as determined by difficulty navigating basic computer tasks during initial screening. – Diagnosed psychiatric affective and non-affective disorders including dissociative disorder, obsessive compulsive disorder, personality disorders, schizophrenia, bipolar disorder – History of significant head trauma resulting in loss of consciousness > 30 min, retrograde amnesia, or post-traumatic concussion syndrome, or any injury with persistent neurological sequelae or known structural brain abnormalities

**Note:** HBA-FAQ = Healthy Brain Ageing Functional Assessment Questionnaire; M@T = Memory Alteration Test; PHQ-9 = Patient Health Questionnaire-9; ToPF = Test of Premorbid Functioning.

**Table 3 mps-09-00130-t003:** Overview of the iCog.X Boost cognitive training program: session structure, cognitive focus, strategies, and home exercises.

Session	Cognitive Focus	Training Activities	Strategies Used	Weekly Home Exercise

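### Tolerability is scored as a share of withdrawals rather than of treated participants, so the verdict depends on how many people leave for other reasons

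*Protocol article*

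**What the plan says.** Section 4.4 (Safety and tolerability) gives the definition: "Tolerability will be operationalised as the proportion of withdrawals that are not attributable to intervention-related AEs". Table 1 uses the same denominator in all three columns. Proceed requires that "≥75% of withdrawals are not attributable to intervention-related adverse events". The middle column reads "60–74% of withdrawals are not attributable to intervention-related adverse events" and the last column "<60% of withdrawals are not attributable to intervention-related adverse events". The text and the table agree, so this is the intended definition and not a slip in one place.

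Section 4.4 says that the Table 1 criteria "will determine whether to proceed to a full-powered definitive trial, while safety is monitored throughout". Section 4.12 is softer and describes the comparison with the thresholds as a guide to progression. Neither section says how rows that disagree are to be combined, sets a minimum number of withdrawals, or covers the case of none.

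Three other provisions matter here. Section 4.7 plans 44 participants, 22 per arm, and states that "An anticipated dropout rate of ~20% has been accounted for". The Retention row of Table 1 gives Proceed below 20% attrition at Week 18, the middle category at 20–30%, and Do Not Proceed above 30%. Section 4.3.3 withdraws participants who miss three sessions in a row and do not respond; these are withdrawals for a reason other than an AE.

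**The concern.** A tolerability criterion should answer how often people who received the intervention could not tolerate it. A share of withdrawals answers a different question: of those who left, how many left for something else. The two can move in opposite directions. Each additional non-AE withdrawal, including those under the missed-session rule, raises the score although tolerability has not changed. Excellent retention leaves a denominator of one or two, so a single event decides the row. The best possible result, no withdrawals at all, gives 0/0.

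This is the only row of Table 1 that names adverse events, and the table is meant to inform the decision on a definitive trial. A row that can rank a lower AE burden below a higher one is a poor basis for that decision.

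**Working it through.** **Inputs.** N = 44, 22 per arm (section 4.7). Anticipated dropout about 20% (section 4.7): 44 × 0.20 = 8.8, about 9 withdrawals. Cut-offs of 75% and 60% for tolerability, 20% and 30% for retention (Table 1). The protocol gives no derivation for the tolerability cut-offs, so there is no figure of its own to reproduce. I apply the rule directly.

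**Formulas.** Let W be total withdrawals and A those due to intervention-related AEs. Tolerability = (W − A)/W. Attrition = W/44, treating every withdrawal as lost by Week 18. AE burden = A/44.

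**Enumeration (no assumed rates).**

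| A | A/44 | Do Not Proceed | Middle category | Proceed |
|---|---|---|---|---|
| 1 | 2.3% | W = 1–2 (0%, 50%) | W = 3 (66.7%) | W ≥ 4 (75% or more) |
| 2 | 4.5% | W = 2–4 (0–50%) | W = 5–7 (60–71.4%) | W ≥ 8 (75% or more) |
| 3 | 6.8% | W = 3–7 (0–57.1%) | W = 8–11 (62.5–72.7%) | W ≥ 12 (75% or more) |

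With W = 0 the score is undefined.

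**Retention row on the same scale.** 8/44 = 18.2% is Proceed; 9/44 = 20.5% to 13/44 = 29.5% is the middle category; 14/44 = 31.8% is Do Not Proceed.

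**The two rows together.**
- A = 1, W = 2: tolerability (2 − 1)/2 = 50%, Do Not Proceed. Attrition 2/44 = 4.5%, so 95.5% are retained.
- A = 2, W = 8: tolerability (8 − 2)/8 = 75%, Proceed. Attrition 18.2%, also Proceed.

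The second trial has twice the AE withdrawals and four times the dropout, and gets the better verdict without leaving the Proceed zone of the Retention row.

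**At the planned dropout (W = 9).** A = 1 gives 8/9 = 88.9% and A = 2 gives 7/9 = 77.8%, both Proceed. A = 3 gives 6/9 = 66.7%, the middle category. A = 4 gives 5/9 = 55.6%, Do Not Proceed.

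**How far unrelated dropout drives the row.** Exact trinomial with n = 44. The withdrawal risks are my assumptions; the protocol gives none by cause. With the AE-withdrawal risk held at 5%:

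| Other withdrawals | P(Proceed) | P(middle) | P(Do Not Proceed) | P(undefined) |
|---|---|---|---|---|
| 5% | 0.20 | 0.18 | 0.61 | 0.01 |
| 10% | 0.39 | 0.29 | 0.32 | <0.01 |
| 15% | 0.57 | 0.29 | 0.15 | <0.01 |
| 20% | 0.71 | 0.23 | 0.06 | <0.01 |

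The 15% line is the one whose total matches the anticipated dropout (5% + 15% = 20%). Over the same four levels of other withdrawals, P(Do Not Proceed) runs 0.33, 0.11, 0.03, 0.01 if the AE risk is 2.3%, and 0.89, 0.69, 0.47, 0.28 if it is 10%. The direction is the same throughout.

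**Participants as denominator.** One AE withdrawal is 1/44 = 2.3% (exact 95% CI 0.1–12.0%), or 1/22 = 4.5% (0.1–22.8%) within one arm. Neither figure changes when others leave, and no AE withdrawals gives 0%.

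**The case against.** The strongest defence is that Table 1 should be read as a whole. A reader might infer that the rule lets a poorly tolerated intervention through; the documents do not support that in general. Proceed on retention needs W ≤ 8, and at W = 8 tolerability allows at most two AE withdrawals. In the middle retention band (W = 9–13) Proceed on tolerability allows at most three. Four AE withdrawals reach 75% only at W = 16, which is 36% attrition and Do Not Proceed on retention. Likewise, high unrelated dropout is no evidence of an overall Proceed: with 5% AE and 30% other withdrawals the tolerability row passes with probability 0.89, but retention is Do Not Proceed with probability 0.72, and both rows are Proceed with probability only 0.01. This part of the defence stands.

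A reader might also infer that one AE withdrawal would end the programme. It fails the row only when total withdrawals are one or two, and at about nine it passes. The protocol does not say that one failing row alone stops progression.

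It can be added that AEs are reviewed for severity and relatedness throughout (sections 4.4 and 4.10), and that early leavers also count in the Retention row and, if they fall below 80% of sessions, in the Adherence row. That is true, but neither row isolates AE-related discontinuation per participant. Nor does the retention limit help with the opposite error, where very good retention makes tolerability fail, or prevent the one-of-two versus two-of-eight ranking.

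**Conclusion.** The point holds in a limited form. As defined, the criterion does not measure tolerability: for a fixed number of AE withdrawals it rises with unrelated dropout, it has no value when nobody withdraws, and it rates one AE withdrawal of two (2.3% of 44) below two of eight (4.5%). These results follow from the protocol's own cut-offs and sample size, taking withdrawals as Week 18 attrition. The probabilities also rest on assumed withdrawal risks: at 5% AE risk, Do Not Proceed on this row falls from 0.61 to 0.06 as other withdrawals go from 5% to 20%.

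The practical damage is greatest when few people withdraw. At the planned dropout the rule behaves more sensibly, and the Retention row limits the risk of passing a poorly tolerated intervention. Because the flaw lies in the stated definition, it is not a detail that a later analysis plan could simply fill in.

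**What to change.** In Table 1 and section 4.4, define tolerability as the proportion of participants who started stimulation and discontinued because of an intervention-related AE, reported overall and by arm. The sponsor should restate the three bands as counts on that denominator and say which denominator, pooled or active arm, decides the row.

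If the sponsor wants to stay close to the present rule at about nine withdrawals, the equivalent pooled counts out of 44 are at most 2 (Proceed), 3 (middle category), and 4 or more (Do Not Proceed), that is 4.5%, 6.8% and 9.1%. These cannot be transferred as percentages to the 22-person active arm: 1/22 is 4.5% and 2/22 is 9.1%, so the middle band would vanish. Bands for one arm need to be set afresh.

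The cost is a wording change in two places and a protocol amendment. No new data are needed, because relatedness of AEs is already reviewed. Recruitment is under way (section 8), so the change should be made and dated before withdrawal outcomes are known; otherwise it will look data-driven.

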**Attrition**			
Retention	<20% participant attrition at final follow-up (Week 18)	20–30% attrition at final follow-up	>30% attrition at final follow-up

**Table 2 mps-09-00130-t002:** Inclusion and exclusion criteria.

Inclusion Criteria	Exclusion Criteria
– Aged 55–85 years – MCI based on Winblad criteria [30] – Subjective cognitive complaints via a semi-structured clinical interview – Objective cognitive decline (M@T score 27–37) OR scoring at least 1.0–1.5 SDs below age-adjusted population norms and/or estimated premorbid ability based on the ToPF – Preserved or minimal iADL impairment based on the HBA-FAQ and study neuropsychologist discretion. – Right-handed (Edinburgh Handedness Inventory) – Fluent in English (reading, writing, speaking) – Normal or corrected-to-normal vision and hearing – Access to a personal desktop or laptop with full internet access	– Prior exposure to TMS within the past 12 months – M@T score < 27 – Study neuropsychologist discretion regarding cognitive and/or functional status based on neuropsychometric performance. – Current symptoms of major depression, defined as a PHQ-9 score ≥ 10 and meeting criteria for a current depressive episode on the MINI interview. – Contraindications to TMS [29]. – Alcohol consumption within 24 h of assessments – Current smokers – Low digital literacy as determined by difficulty navigating basic computer tasks during initial screening. – Diagnosed psychiatric affective and non-affective disorders including dissociative disorder, obsessive compulsive disorder, personality disorders, schizophrenia, bipolar disorder – History of significant head trauma resulting in loss of consciousness > 30 min, retrograde amnesia, or post-traumatic concussion syndrome, or any injury with persistent neurological sequelae or known structural brain abnormalities

**Note:** HBA-FAQ = Healthy Brain Ageing Functional Assessment Questionnaire; M@T = Memory Alteration Test; PHQ-9 = Patient Health Questionnaire-9; ToPF = Test of Premorbid Functioning.

**Table 3 mps-09-00130-t003:** Overview of the iCog.X Boost cognitive training program: session structure, cognitive focus, strategies, and home exercises.

Session	Cognitive Focus	Training Activities	Strategies Used	Weekly Home Exercise
1	Introduction to Cognitive Training	Platform familiarisation, delayed matching, auditory memory recall	Chunking, retrieval practice, visual imagery	Introduce cognitive training principles, establish baseline, and teach foundational memory strategies
2	Attention & Processing Speed	Visual search, dual-task (memory + attention)	Focused attention, dual-task training	Improve selective attention, processing speed, and task coordination
3	Memory (Auditory & Visual)	Word-pair recall, story recall, visual search	Association elaboration, Method of Loci	Strengthen encoding and retrieval processes, enhance associative memory
4	Reasoning (Inductive & Deductive)	Pattern recognition, rule identification	Logical deduction, analogy-based reasoning	Develop reasoning strategies and cognitive flexibility
5	Problem-Solving & Decision-Making	Real-life problem-solving tasks, strategic planning exercises	Stepwise problem-solving, decision trees	Enhance problem-solving skills and apply strategies to real-world situations
6	Attention (Divided & Selective)	N-back task, divided attention in ADLs	Prioritization, response inhibition	Strengthen divided attention and working memory
7	Complex Attention & Executive Functioning	Dual-task (memory + attention)	Task-switching, cognitive flexibility	Reinforce attention strategies and adaptive executive functioning
8	Visual Memory	Visual memory in ADLs	Mnemonic reinforcement, environmental cues	Generalise memory strategies to everyday activities
9	Auditory Memory	Auditory recall tasks in ADLs	Active listening, verbal rehearsal	Improve auditory memory
10	Dual-Task Training	Memory + attention, ADL-based attention	Divided attention practice, strategy switching	Reinforce multi-tasking and integration of memory and attention skills
11	Advanced Reasoning & Problem-Solving	Inductive reasoning, problem-solving tasks	Hypothesis testing, inferential thinking	Apply problem-solving techniques to novel contexts
12	Decision-Making & Planning	Deductive reasoning, complex decision-making in ADLs	Mental simulation, pre-decision frameworks	Strengthen logical reasoning and structured decision-making
13	Integrated Problem-Solving	Dual-task (reasoning + memory), problem-solving in ADLs	Multi-step problem-solving, adaptive reasoning	Apply advanced problem-solving strategies across domains
14	Strategy Consolidation	Recap of all cognitive strategies, transfer to daily activities	Meta-cognitive reflection, self-monitoring	Ensure generalisation and long-term retention of trained skills

**Table 4 mps-09-00130-t004:** Schedule of activities for screening, baseline, endpoint, and follow-up timepoints.

Assessment Schedule		Screening (−4 wks)	Baseline (0 wks)	Post-iTBS (1 wk)	Midpoint (5 wks)	Endpoint (10 wks)	Follow-Up (18 wks)
**Screening**	Inclusion/Exclusion Criteria	X					
	Informed Consent	X					
	GHQ	X					
	Premorbid Function (ToPF)	X					
	M@T	X				X	X
	CVLT-II Short Form	X					
	HBA-FAQ	X	X			X	X
	MINI	X					
